## Abstract

**Background/Objectives:** Chronic kidney disease and mineral bone disorders (CKD-MBD) are frequently associated with an increased risk of both vascular calcifications (VCs) and bone fractures (BFs). The complex pathogenesis of VCs and BFs involves various factors such as calcium overload, phosphate imbalance, and secondary hyperparathyroidism. Key players, such as the vitamin K-dependent proteins (VKDPs) matrix Gla protein (MGP) and bone Gla protein (BGP), have pivotal roles both for VCs and BFs. The VIKI study highlighted that hemodialysis patients treated with calcimimetics had higher levels of total BGP and MGP compared to those untreated, suggesting a potential protective effect of these drugs on BFs and VCs beyond the beneficial effect of reducing PTH levels. **Methods:** ETERNITY-ITA is a multi-center, comparative effectiveness, observational, longitudinal study that will enroll 160 hemodialysis patients (80 patients treated with Etelcalcetide and 80 age- and sex-matched patients treated with calcitriol or vitamin D analogs). Nephrologists will tailor the target dose of Etelcalcetide on an individual level to achieve the KDIGO PTH target. In the Etelcalcetide-treated group, the addition of calcitriol will be allowed when required by clinical practice (for correction of hypocalcemia). **Conclusions:** This study will evaluate the real-world effect of Etelcalcetide on VKDP levels, such as BGP and MGP, at 3, 9, and 18 months from baseline. The resulting preservation of vascular and bone health will be assessed for the first time by examining aortic and iliac artery calcifications and vertebral fractures, respectively.

## 1. Introduction

Vascular calcifications (VCs) are common complication of CKD mineral and bone disorders (CKD-MBD). In CKD patients, the prevalence of aortic calcification is higher than in the general population and VCs were found to be associated with a higher prevalence of bone fractures (BFs) [1]. The pathogenesis of VC in CKD patients is multifactorial, with calcium and phosphate overload and secondary hyperparathyroidism (HPT) among the most relevant etiological factors [2]. Calcification inhibitors are also important determinants of VCs [3]. A vitamin K-dependent protein (VKDP), such as matrix Gla protein (MGP), is characterized not only by five sites of carboxylation (c-MGP) but also by the phosphorylation of three serine residues (p-c MGP, through the enzyme casein kinase) [4,5], which seem to regulate protein secretion into the extracellular environment [5]. The main function of MGP is associated with the carboxylate form, which makes it a strong inhibitor of vascular calcifications, probably due to its interaction with bone morphogenetic protein 2 (BMP-2: a powerful osteoinductive protein), which transforms vascular smooth muscle cells (VSMCs) into osteoblast-like cells [6]. c-MGP binds calcification crystals in blood vessels, forming vesicles and apoptotic bodies and preventing both calcium phosphate precipitation and the trans-differentiation of VSMCs into an osteogenic phenotype [5]. Another remarkable VKDP is bone Gla protein (BGP), which is mainly secreted by osteoblasts and in small quantities even by chondrocytes [7,8]. It has three carboxylated sites, making it active in its main bone mineralization action and allowing the interaction between the calcium-binding Gla residues and the calcium ions of hydroxyapatite, forming hydroxyapatite crystals. Indeed, BGP also acts as an inhibitor of bone mineralization, regulating mineral maturation [8].

The current paradigm for reducing the risk of vascular calcification (VC) development and progression revolves around the reduction of parathyroid hormone (PTH), calcium, and phosphorus. In particular, the recent Kidney Disease Improving Global Outcomes (KDIGO) guidelines recommend targeting PTH levels to a range between 2–9 times the upper normal limit [2]. In this scenario, Etelcalcetide emerges as a novel synthetic peptide that binds the calcium-sensing receptor-enhancing activation of the receptor itself through extracellular calcium and at the same time decreases PTH secretion in parathyroid cells [9]. Experimental studies [1] and human studies [7] have shown that oral calcimimetics use prevents vascular calcification by an MGP-mediated mechanism (increasing MGP serum levels) not seen with the use of vitamin D or its analogs.

The main aim of this study will be to assess whether Etelcalcetide, compared to vitamin D or vitamin D analog treatments, increases the levels of vitamin K-dependent proteins (VKDPs) such as bone Gla protein (BGP) and matrix Gla protein (MGP) at 3, 9, and 18 months from baseline, resulting in proper bone mineralization and inhibition of vascular calcification. The secondary aims include evaluating, at 18 months, whether treatment with Etelcalcetide decreases the progression of vascular calcification (in the aorta and iliac arteries) and vertebral fractures.

## 2. Methods

### 2.1. Study Design

This is a national, multi-center, comparative effectiveness, observational, longitudinal study with no predefined interference on drug dosing by the investigators. Nineteen Italian centers will be involved. In each center, 14 patients will be screened for eligibility and about 10–12 patients are scheduled to be enrolled. This study will enroll 160 hemodialysis patients (80 patients treated with Etelcalcetide and 80 age- and sex-matched patients treated with calcitriol or a vitamin D analog, paricalcitol) (Figure 1).

Given the observational nature of this study, the investigators will not recommend target goals of Etelcalcetide treatment. The treating nephrologists will tailor their target dose of Etelcalcetide on an individual-level patient basis in order to achieve the KDIGO PTH target levels. In the Etelcalcetide-treated group, the addition of calcitriol is allowed when required by current clinical practice (for correction of hypocalcemia). Blood samples for the measurement of specific biomarkers will be collected in concomitance with the routine blood sampling scheduled in each center. At baseline, all relevant demographic, clinical, and biochemical data will be collected in compliance with the privacy laws of the European Union. The study design is illustrated in Figure 2.

### 2.2. Ethical Considerations

Written informed consent will be obtained from each participant. The study is registered at clinicaltrials.gov: NCT 06352957. This study will be conducted according to the Helsinki declaration.

## 3. Study Objectives and Aims

### 3.1. Main Outcome Measures

The main outcome measure is the comparison of VKDP levels between patients treated with Etelcalcetide and those treated with vitamin D or vitamin D analogs. The longitudinal changes of the following VKDPs (measured at baseline and after 3, 9, and 18 months) will be compared between the two groups: total MGP, dephosphorylated-undercarboxylated MGP (dp-ucMGP), total BGP, and undercarboxylated BGP (ucBGP).

### 3.2. Other Outcome Measures

The following bone vascular marker levels will be considered: calcium, phosphate, magnesium, ALP, PTH, 25(OH)D, procollagen I intact N-terminal or P1NP, C-terminal telopeptide or CTX, tartrate-resistant acid phosphatase 5b or TRAP 5bC-Terminal to Intact, bone-specific alkaline phosphatase (BSAP), fibroblast growth factor 23 or cFGF23 and iFGF23, klotho and soluble α-klotho, sclerostin and bioactive sclerostin, DKK1, fetuin-A, zinc, and irisin.

The analysis will assess whether Etelcalcetide will affect the levels of the above-mentioned biomarkers over time.

2.Evaluation of serum calcification propensity using the T50 test [10,11].3.Changes from baseline of the following anemia marker levels are considered: hemoglobin (Hb), hematocrit (Ht), plates (PLTS), reticulocytes, iron, ferritin, transferrin, and transferrin saturation. This is to test whether 3, 9, and 18 months of treatment with Etelcalcetide improves anemia status (e.g., reduced EPO and/or iron doses).4.Changes from baseline of the following dialysis routine biomarkers: albumin, KT/V, aluminum, C-reactive protein (CRP), cholesterol, triglycerides, cholesterol HDL, and cholesterol LDL.

The analysis will assess whether Etelcalcetide will affect the levels of the above-mentioned biomarkers over time.

5.Changes from baseline prevalence VCs (aorta and iliac arteries) measured using a lateral dorsal lumbar spine X-ray [time frame: 18 months].

To test whether 18 months of treatment with Etelcalcetide reduces VC progression.

6.Changes from the baseline prevalence of vertebral fractures (VFs, quantitative vertebral morphometry using dedicated software, Optasia Medical SpineAnalyzer 4.0, version 4.0.2.19) measured using a lateral dorsal lumbar spine X-ray [time frame: 18 months].

To test whether 18 months of treatment with Etelcalcetide reduces VF progression.

7.Changes from baseline total hip, femoral, and neck bone mass density (BMD), measured by dual-energy X-ray absorptiometry (DEXA), including a trabecular bone score (TBS) when available. To test if 18 months of treatment with Etelcalcetide improves BMD and TBS.8.To assess the relationship of bone vascular biomarkers and clinical outcomes: VFs and VCs.9.To compare a novel quantitative computer-assisted scoring method for vascular calcifications with a three-dimensional assessment from CT data [12,13].10.To evaluate the effect of Etelcalcetide on cardiovascular events and all-cause mortality.11.To evaluate the safety of Etelcalcetide and drug interactions.

### 3.3. Inclusion Criteria

Patient has provided informed consent.Patient is 18 years of age or older of both sexes.Patients receiving maintenance HD three times per week (Kt/V >1.2).Parathyroid hormone concentrations >500 ng/l at screening, or if parathyroidectomy is planned or expected, Ca >8.3 mg/dL.Will be considered in the exposed group:
patients who have started Etelcalcetide within 1 month of study enrolment;patients naïve to intravenous calcimimetics use;patients who have suspended oral calcimimetics for at least 1 month;patients who are not responding to or non-compliant with treatment with calcitriol.
In the unexposed group, patients being treated with calcitriol or vitamin D analogs and who are age- (±2 years) and sex-comparable (matching) to those in the exposed group will be considered.Native vitamin D can be used in both groups and should be administered to target a 25(OH)D level >30 ng/mL.Dialysate calcium concentration must be stable for at least 4 weeks prior to screening laboratory assessments.Patient must have severe HPT as defined by two laboratory screening pre-dialysis serum PTH values >500 pg/mL, measured on two consecutive lab checks prior to entering the study. PTH levels should be standardized as reported elsewhere [14].Total alkaline phosphatase greater than the normal range, or even within the normal range but if greater than the tertile of the reference range for the assay.Patients will be eligible only if they will show at least moderate aorta VCs [15] and/or iliac artery VCs and at least a mild VF [16,17].

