### 3.4. Exclusion Criteria

Previous treatment with oral calcimimetics (cinacalcet) must have been suspended for at least 30 days. Recent start of calcimimetics (Etelcalcetide) is acceptable, but patients are excluded if the treatment lasts for more than 1 month.Patients who received a bisphosphonate, denosumab, or teriparatide during the 12 months prior to screening.Patients who underwent parathyroidectomy in the 6 months before the start of the study or if the procedure is scheduled soon.Scheduled kidney transplant during the study period or anticipated living donor evaluation within three months of recruitment.Patients with unstable medical conditions based on medical history, physical examinations, and routine laboratory tests, or otherwise deemed unstable in the judgment of the Investigator.Having metabolic bone diseases not related to the kidney (i.e., Pagets, Osteogenesis Imperfecta).With severe untreated hyperthyroidism.With malignancy within the last 3 years (except non-melanoma skin cancers or cervical carcinoma in situ).Patients pregnant or nursing.Patients with Long QT Syndrome.Patients who are unlikely to be available to complete all protocol-required study visits or procedures, and/or to comply with all required study procedures to the best of the patient’s and Investigator’s knowledge.

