### 4.2. Data Analysis

Normally distributed variables will be summarized as means and standard deviations, non-normally distributed variables as medians and interquartile ranges, and categorical data as absolute numbers and percentages. At baseline, the between-groups comparisons will be performed using the independent *t*-Test, the Mann–Whitney U Test, or the Chi-squared test, as appropriate. The between-groups comparisons of repeated measurements of biomarkers (as continuous variables) over time will be performed by linear mixed models (LMM) or generalized estimating equations (GEE). No imputation method of missing values will be applied. In these analyses, the effect of the exposure to Etelcalcetide in treated patients versus those untreated will be preliminarily investigated by including the group variable, the time, and the interaction term between the group variable and time. The effect of potential confounders on the effectiveness of Etelcalcetide on the study outcomes will be further investigated by adjusting for all potential confounders, including medications, by multiple regression models. Sensitivity analysis by applying the propensity score approach will be also performed. The primary analysis will be conducted considering the patients as belonging to the treatment arm they had at the beginning of observation. A secondary analysis will also be performed taking into account any cross-over. Survival analyses will be performed using the Kaplan–Meier and Cox regression methods. All statistical analyses will be performed using a standard statistical package (STATA 16, StataCorp. Stata Statistical Software. College Station, TX, USA).

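### Exposed patients may enter up to a month after their first Etelcalcetide dose, and nothing shown requires the baseline VKDP sample to be pre-dose, so the main change contrast can miss early response

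*Protocol article*

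**What the plan says.** **Entry window.** Section 3.3 lists as exposed "patients who have started Etelcalcetide within 1 month of study enrolment". That wording alone could mean a start shortly before or shortly after enrolment. Section 3.4 settles that a prior start is allowed: "Recent start of calcimimetics (Etelcalcetide) is acceptable, but patients are excluded if the treatment lasts for more than 1 month".

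**Main outcome.** Section 3.1 states: "The longitudinal changes of the following VKDPs (measured at baseline and after 3, 9, and 18 months) will be compared between the two groups". The aim in Section 1 also counts the three follow-up visits from baseline, not from first dose.

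**Sampling.** Section 2.1 states: "Blood samples for the measurement of specific biomarkers will be collected in concomitance with the routine blood sampling scheduled in each center". This ties the draw to the centre's routine, not to the first dose. Section 5 lists the VKDPs among the markers assayed centrally, apart from the routine tests done locally.

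**Model.** Section 4.2 specifies a mixed model or GEE "including the group variable, the time, and the interaction term between the group variable and time".

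**Controls.** Section 3.3 takes age- and sex-matched patients already on calcitriol or a vitamin D analog, with no limit on how long they have been on it.

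**The concern.** A change from baseline measures the whole drug effect only if the baseline is taken before the drug. Here some exposed patients can have had up to a month of treatment when the baseline sample is drawn. Whatever their VKDPs did in that month is then subtracted from their change. In the group-by-time model it goes into the group term and out of the interaction.

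The time scale also shifts. Section 3.2 describes the visits, in its anemia item, as 3, 9 and 18 months on treatment. For patients who started before enrolment they can fall later than that.

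The main contrast of the study is at stake, and the gap cannot be filled afterwards. A VKDP value before the first dose exists only if a sample was drawn for it. The VKDPs are not among the routine tests, so local records cannot be expected to hold one.

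**Working it through.** **The plan's own figure.** The only sample-size figure that can be recomputed is the number of observations: (80 + 80) patients × 4 visits = 640, as Sections 4.1 and 7.1 state. There is no power calculation to reproduce; Section 4.1 calls the size pragmatic.

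**Time on drug.** Let m be the months on Etelcalcetide at baseline, between 0 and 1 (Sections 3.3 and 3.4). At baseline and the three follow-up visits, time on drug is m, 3 + m, 9 + m and 18 + m. At the limit m = 1 this is 1, 4, 10 and 19 months, against a nominal 0, 3, 9 and 18.

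**Effect on the change.** The article gives no VKDP time course, so one is assumed: f(t) = E(1 − exp(−t/τ)), with E the full effect and τ the time constant in months. The change measured at visit v is

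f(v + m) − f(m) = exp(−m/τ) × f(v).

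The retained share is exp(−m/τ) at every visit, so under this curve the loss does not fade by month 18.

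- Loss at a full month (m = 1): 1 − exp(−1/τ).
- Average loss with m uniform on 0 to 1: b = 1 − τ(1 − exp(−1/τ)).
- If only a share p of the exposed had already started: p × b.
- Sample-size factor for equal power, SD unchanged: 1/(1 − p × b)².

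| τ (months) | Loss at m = 1 | Average loss, all started | Average loss, half started | Size factor, all / half |
|---|---|---|---|---|
| 1 | 63% | 37% | 18% | 2.50 / 1.50 |
| 3 | 28% | 15% | 7.5% | 1.38 / 1.17 |
| 8.7 (half-time 6) | 11% | 5.6% | 2.8% | 1.12 / 1.06 |
| 17.3 (half-time 12) | 5.6% | 2.8% | 1.4% | 1.06 / 1.03 |

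Example for τ = 1: b = 1 − 1 × (1 − 0.368) = 0.368, and 1/(0.632)² = 2.50. For τ = 3: b = 1 − 3 × (1 − 0.7165) = 0.150, and 1/(0.850)² = 1.38. Onset faster than τ = 1 would lose more.

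**Other response shapes, at m = 1.** The retained share at the 3, 9 and 18 month visits is:

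- complete by month 1: 0% at all three;
- linear to a plateau at 3 months: 67% at all three;
- linear to a plateau at 6 months: 100%, 83%, 83%;
- linear to 24 months, so still rising at month 19: 100% at all three;
- delayed sigmoid, t³/(t³ + 6³): 202%, 106%, 100%, because the nominal 3-month visit falls at 4 months on drug.

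The direction therefore depends on the shape. Attenuation needs a response that starts in the first month and then slows.

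**The case against.** A reader might infer that the design is known to understate the drug effect. The article does not support that. It reports no VKDP time course, and the linear and delayed curves show no attenuation. What can be said is conditional. The first follow-up at 3 months shows only that the investigators look for an early response.

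Section 3.1 also names a comparison of VKDP levels between groups. An unadjusted comparison of follow-up levels would not be attenuated, and this stands. Without randomization, however, that comparison gives up control of baseline VKDP differences, and the same section and the model in Section 4.2 turn to change over time.

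Figure 2, which is said to show blood sampling over time, is not available here, and the article condenses a fuller protocol. A pre-dose rule could stand there. Even so, the eligibility text as written admits patients for whom a pre-dose study sample may be impossible.

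It would also be too strong to call the control baseline clean or the loss beyond any modelling. Controls are on treatment at baseline too, for an unlimited prior time, so time zero is not aligned between the groups. Patients sampled before their first dose would supply pre-dose values, and with first-dose dates time since first dose could be modelled, under assumptions.

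Finally, the larger size factors (2.50 and 1.38) suppose that every exposed patient had already started. That share is unknown, and with no stated power the factors are only relative.

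**Conclusion.** The timing defect is in the text: exposed patients may be up to one month on drug at entry, the main outcome is change from a study baseline, and nothing shown requires that baseline to be pre-dose. If response begins in the first month and then levels off, the group-by-time contrast is biased toward no effect.

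The size cannot be derived from the article. For time constants of 1 to 3 months and even start dates, the average loss runs from 37% down to 15% if all exposed patients had started, about half that if half had, and to a few percent for slow onset. These figures rest on the assumed curve and the assumed share of prior starters.

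The documents do not support a claim of certain understatement, or that already-started patients must be excluded. The point should be settled before enrolment, because a missing pre-dose sample cannot be obtained later.

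**What to change.** 1. In Sections 3.1 and 3.3, define the VKDP baseline as a central-laboratory sample drawn before the first Etelcalcetide dose wherever the patient can be identified at prescription.
2. Record the first-dose date for every exposed patient and the time on current therapy for every control.
3. Count the 3, 9 and 18 month visits from first dose, or model time since first dose, and make the wording in Section 3.2 agree.
4. Prespecify an analysis of the main change outcome restricted to exposed patients with a pre-dose sample and their matched controls, reported alongside the full-cohort result.

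This governs sampling and analysis, not when or how patients are treated. Already-started patients can stay in the study, so their matched controls are not stranded. The cost is somewhat earlier identification of exposed patients, which is harder because eligibility also depends on X-ray findings, and a smaller, less precise pre-dose subset. No visits or assays are added to the schedule.

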### 3.4. Exclusion Criteria

Previous treatment with oral calcimimetics (cinacalcet) must have been suspended for at least 30 days. Recent start of calcimimetics (Etelcalcetide) is acceptable, but patients are excluded if the treatment lasts for more than 1 month.Patients who received a bisphosphonate, denosumab, or teriparatide during the 12 months prior to screening.Patients who underwent parathyroidectomy in the 6 months before the start of the study or if the procedure is scheduled soon.Scheduled kidney transplant during the study period or anticipated living donor evaluation within three months of recruitment.Patients with unstable medical conditions based on medical history, physical examinations, and routine laboratory tests, or otherwise deemed unstable in the judgment of the Investigator.Having metabolic bone diseases not related to the kidney (i.e., Pagets, Osteogenesis Imperfecta).With severe untreated hyperthyroidism.With malignancy within the last 3 years (except non-melanoma skin cancers or cervical carcinoma in situ).Patients pregnant or nursing.Patients with Long QT Syndrome.Patients who are unlikely to be available to complete all protocol-required study visits or procedures, and/or to comply with all required study procedures to the best of the patient’s and Investigator’s knowledge.

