## 7. Discussion

In addition to its known suppressive effect on PTH, Etelcalcetide has demonstrated additional benefits in recent studies, both experimental and human. In rats, it has been shown to preserve cortical bone structure and bone strength by lowering PTH in subtotal Nx rats with established SHPT [19,20]. In humans, it has been found to improve areal bone mineral density and trabecular quality in the central skeleton, always by lowering bone turnover without affecting bone material properties, thereby reducing the risk of fractures [21,22]. A recent meta-analysis comparing various calcimimetics has shown that Etelcalcetide is the most efficacious calcimimetic agent for lowering serum PTH levels but highlighted side effects such as hypocalcemia, nausea, and vomiting. Cinacalcet ranked worst for nausea and had somewhat lower effectiveness, while Evocalcet (in use in Asian populations) had lower effectiveness for decreasing PTH levels but was associated with fewer adverse effects [23].

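### Exposed patients may enrol up to one month after their first Etelcalcetide dose, so early harms and early stoppers can be missed and the safety estimate understated as a risk from first dose

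*Protocol article*

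**What the plan says.** Section 3.3 (Inclusion Criteria) lists among the exposed "patients who have started Etelcalcetide within 1 month of study enrolment". Section 3.4 (Exclusion Criteria) confirms the rule from the other side: "Recent start of calcimimetics (Etelcalcetide) is acceptable, but patients are excluded if the treatment lasts for more than 1 month". Section 3.3 also lists "patients naïve to intravenous calcimimetics use", so some exposed patients may enter with no earlier dose.

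Section 4.2 (Data Analysis) fixes group membership at entry: "The primary analysis will be conducted considering the patients as belonging to the treatment arm they had at the beginning of observation".

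Item 11 of section 3.2 (Other Outcome Measures) is "To evaluate the safety of Etelcalcetide and drug interactions". The Discussion cites a meta-analysis of calcimimetics that "highlighted side effects such as hypocalcemia, nausea, and vomiting". Section 2.1 expects hypocalcemia in the Etelcalcetide group, because it allows calcitriol to be added to correct it.

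**The concern.** A drug's safety is normally understood as the risk from the first dose onward. Here follow-up of an exposed patient can begin up to a month later, which has two consequences. In a patient who is enrolled, a harm between first dose and enrolment comes before observation. A patient who starts, has a harm and stops before enrolment is not on Etelcalcetide when observation begins and is not counted as exposed.

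Both remove events from the same period, the first weeks of treatment. The first scheduled biomarker visit after baseline is at 3 months (section 3.1), so no study visit covers that period. The Limitations section (7.3) names confounding and offers covariate adjustment. Adjustment does not restore events that precede entry, or patients who never enter. At stake is how item 11 can be read: a reader could take a figure from patients already some weeks into treatment as the risk a new starter faces.

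**Working it through.** **The plan's own figures.** The article gives no harm rate, onset time or share enrolled after first dose, so there is no safety figure to reproduce. Its one derived count reproduces (80 × 4 + 80 × 4 = 640 observations) but has no bearing here.

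**Does the rule produce the gap?**

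1. Sections 3.3 and 3.4 both allow a lag of 0 to 1 month between first dose and enrolment.
2. Section 4.2 sets the arm by treatment at the beginning of observation.
3. Together, someone who started and stopped within that lag is not in the exposed arm. No single sentence says this; it follows from the three sections.
4. At most, all 80 exposed patients enter at one month. Treated time is then 80 × (18 + 1) = 1,520 patient-months, of which 80 × 1 = 80 (80/1,520 = 5.3%) precede observation. All 80 are first-month time.

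**Share of events lost among patients already started.** Let f be the share of 18-month first events that falls in month 1 (an assumption). If entry is spread evenly over the month, and so are events within it, half of the month-1 events precede entry and the loss is f/2. If entry is at one month, the loss is f. Across the exposed group the loss is multiplied by p, the share enrolled after their first dose (also an assumption).

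| f | already started (p = 100%) | p = 50% | p = 25% |
|---|---|---|---|
| 1/18 = 5.6% (events evenly spread) | 2.8-5.6% | 1.4-2.8% | 0.7-1.4% |
| 30% | 15-30% | 7.5-15% | 3.8-7.5% |
| 50% | 25-50% | 12.5-25% | 6.3-12.5% |

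With p = 0 the loss is zero.

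**Effect on an estimated risk.** Let R be the true risk from first dose, L the part of the month elapsed at enrolment, and m = R × f × L × p. If early events go uncounted in enrolled patients, with no later event counted in their place, the observed risk is R − m. If those patients stop and are never enrolled, it is (R − m)/(1 − m). With R = 30% (assumed) and L = 1:

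- f = 1/18, p = 50%: m = 0.0083; observed 29.2% or 29.4%.
- f = 50%, p = 50%: m = 0.075; observed 22.5% or 0.225/0.925 = 24.3%.
- f = 50%, p = 100%: m = 0.15; observed 15.0% or 0.15/0.85 = 17.6%.

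Because m ≥ 0 and R ≤ 1, neither expression can exceed R. The error in the risk from first dose is zero or downward.

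**The case against.** The article gives safety one line. Event definitions, time origin and collection window belong in the full protocol, and their absence here is no fault. The full protocol may collect pre-enrolment events for enrolled patients. This stands, but it would repair only part of the problem: starters who stopped before enrolment stay outside the cohort whatever is collected on those inside it. The loss comes from the entry rule as stated, not from an omitted detail. It is also true that the one-month cap limits the selection and that harms arising later, during individual dose tailoring, are still observed.

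Four stronger readings are tempting but not supported.

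- A reader might infer that the whole exposed cohort has been selected for tolerating the drug. The category of patients naïve to intravenous calcimimetics means some may be followed from their first dose.
- A reader might infer that the comparison of cardiovascular events and deaths (item 10) is biased in favour of Etelcalcetide. The unexposed are current users of calcitriol or vitamin D analogs with no stated limit on earlier treatment, so they too are conditioned on having survived and tolerated therapy, perhaps for longer. The direction between groups is not shown. Counting time from the first Etelcalcetide dose would give them no matching origin, and it would not recover early stoppers.
- A reader might infer that the calcium floor screens out patients already hypocalcemic on the drug. The wording, "or if parathyroidectomy is planned or expected, Ca >8.3 mg/dL", leaves open to whom it applies, and nothing says the sample is taken on treatment.
- A reader might take a loss of 15-50% as the expected size. That range needs f of 30-50% and covers only patients already started.

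**Conclusion.** The point holds for the descriptive safety objective, item 11, and only for patients who had their first dose before enrolment or who stopped before they could enrol. For them the entry rule can leave the risk from first dose correct or too low; in neither case worked above is it too high.

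The documents do not determine the size. Among already-started patients, enrolled follow-up misses about 3-6% of 18-month first events if these are evenly spread, and 25-50% if half of them fall in month 1. Across the exposed group the loss is smaller in proportion to the share enrolled after first dose. These figures rest on assumed values of f and on even spread within the month; events concentrated early in that month would push the loss from f/2 towards f. No conclusion follows for item 10, for any between-group comparison, or for the main vitamin K-dependent protein outcome.

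**What to change.** For the safety objective only:

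1. Record the date of the first Etelcalcetide dose for every exposed patient.
2. For those enrolled after it, collect calcium values and adverse events between first dose and enrolment from the dialysis record. Calcium is already a routine local measurement (section 5).
3. At each of the nineteen centers, keep an anonymous log of all patients starting Etelcalcetide during recruitment, with the number who stopped before enrolment and the reasons.
4. Report safety from first dose alongside that log, and separately for patients enrolled at or before their first dose, whose results do not depend on the gap.

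The cost is a short record review for exposed patients already started, covering at most one month each, and one log per site. It needs no added visits or tests and no change to treatment. The log should start with recruitment, since patients who stopped early are hard to trace afterwards.
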